## Abstract

**Introduction:**

: Although there are various therapeutic methods for the treatment of knee osteoarthritis, each has its advantages and shortcomings, and a definitive treatment method is yet to be determined. This pilot study is designed to obtain basic data for a further large-scale trial as well as provide information about the feasibility of thread embedding acupuncture (TEA) with polydioxanone thread in knee osteoarthritis patients.

**Methods and analysis::**

This study is a clinical trial to evaluate the efficacy and safety of TEA for knee osteoarthritis. Forty participants will be recruited at the hospital and after randomization into 2 groups of 20 (experimental and control); they will be treated for 6 weeks. The experimental group will receive TEA treatment 6 times (1 time/week) in 6 weeks on 14 defined knee areas, and the control group, acupuncture treatments 12 times (2 times/week) in 6 weeks on 9 defined acupuncture points. The visual analogue scale (VAS) will be used for the primary efficacy assessment and Short-form McGill Pain Questionnaire (SF-MPQ), Western Ontario and McMaster Universities Osteoarthritis Index (WOMAC) will be used for the secondary efficacy assessment. The follow-ups before clinical trial, 3 weeks after procedure, 6 weeks after procedure, and 4 weeks after the end of procedure will be done to compare the degree of pain with the control group, which received the acupuncture treatment.

**Conclusion::**

The trial based on this study will provide clinical information on the efficacy and safety of TEA treatment on knee osteoarthritis.

**Trial registration number::**

KCT0004844

## Introduction

1

Osteoarthritis is a primarily noninflammatory, degenerative joint disease characterized by progressive loss of articular cartilage, subchondral bone sclerosis, osteophyte formation, changes in the synovial membrane, and an increased volume of synovial fluid with reduced viscosity and hence changed lubrication properties.^[1]^ Knee osteoarthritis is the most common among all degenerative arthritis and the key cause of chronic disorders. The prevalence rate of knee osteoarthritis increases with age and weight.^[2]^ At around age 40, approximately 25% of the entire adult population displays motor disorders in the joints and approximately 13% and 10% of women and men over the age of more than 60 years, respectively, are afflicted with knee osteoarthritis.^[3]^

Although there are various therapeutic methods for the treatment of knee osteoarthritis in modern medicine, including life management, exercise therapy, drug treatment and surgery, and so on, each has its respective advantages and shortcomings, from the perspectives of compliance of the patients, efficacy, and side effects, and a definitive treatment method is yet to be determined.^[4]^ In particular, pharmacological treatment includes the use of aspirin, acetaminophen and nonsteroidal anti-inflammatory drugs (NSAIDs), and steroid injection into the joint. However, analgesics can induce diseases of the gastrointestinal tract such as intestinal hemorrhage, indigestion and vomiting,^[5]^ as well as hypersensitive reactions such as rash. Meanwhile, injection of steroid into the joint can help achieve temporary alleviation of the symptoms but needs to be used with utmost precautions due to the risks of destruction and infection of cartilage if injected repetitively within short periods of time.^[6]^

In Korean medicine, there have been relevant research and basic studies, including acupuncture,^[7]^ pharmacopuncture treatment,^[8]^ herbal medicine treatment,^[9]^ and moxibustion treatment,^[10]^ on knee osteoarthritis with results that demonstrate the efficacy of such treatments. Thread embedding acupuncture (TEA) among Korean medicinal therapies is an acupoint stimulation therapy being newly highlighted as a type of acupoint embedding therapy with an increase range of applications in recent years.^[11]^ Thread embedding treatment maximizes stimulation by inserting embedded threads into the acupoint, percutaneous layer, superficial muscles, meridian system, or areas that induce pain by means of needle retention action.^[12]^ In addition, it activates the meridian system, supply nutrients to muscles and peripheral nerves, and strengthening cell immunity.^[13,14]^

However, few clinical studies have been done on TEA and most of them are case studies.^[15]^ Therefore, this is a clinical study to investigate the efficacy and safety of TEA by comparing its effects with those of the ordinary acupuncture group in knee osteoarthritis, through a randomly allocated clinical trial.

## Methods and analysis

2

### Objective

2.1

The aims of this pilot trial are to compare pain improvement between the TEA and the acupuncture groups with knee osteoarthritis, to establish the feasibility of future TEA research, and to provide clinical evidence of the basic data before the large sample size study.

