### Study design

2.2

We will conduct a single-institution, randomized controlled pilot trial to compare the efficacy and safety of TEA with acupuncture on knee osteoarthritis.

A total of 40 participants diagnosed with knee osteoarthritis will be recruited from Daegu Oriental Hospital through advertisements. The recruitment period will run from the date of Institutional Review Board (IRB) approval to December 31, 2020. The investigator will have an interview with every potential participant by telephone and schedule screening visits. During the screening visits, every potential participant will be informed in details, ample opportunities to know about all foreseeable results will be given, and written consents will be obtained from the participants. A random assignment will be performed to divide the experimental group and the control group. The probability of being assigned to the 2 groups will be the same. The experimental group will receive TEA treatment on the knee region. The control group will receive commonly used acupoints for knee osteoarthritis treatment. The visit date will be recognized 3 days before and after the visit date and carry on for 10 weeks. A flowchart of the study is illustrated in Fig. 1, and the clinical trial schedule for treatment and outcome measurement is presented in Table 1.

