#### Randomization

2.3.3

Block randomization will be performed, the size of the block will be 4, then the experimental and control groups will be 2:2 for each block, the randomization codes will be assigned between the groups, and will be proceeded as a pilot study. Random numbers were generated by an independent statistician. Sealed opaque assignment envelopes were used for allocation concealment. Once the clinical trial starts, each participant, who meets the selection criteria, will be assigned to the experimental and control groups according the randomization code.

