#### Sample size

2.10.1

This clinical trial is a pilot study, and will prepare for the primary confirmation stage and basic data about prudence in the study and clinical results before the large sample size study. Hence, rather than following the separate sample counting criteria, 20 participants were selected (20% dropout rate considered) for the experimental and control groups.

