#### Statistical analysis

2.10.2

This statistical analysis is based on “Clinical Trial Statistics Guide (KFDA, 2000)” and the statistical package used is IBM SPSS Win ver. 19.0. The last observation carried forward method is used for missing data from drop-outs. For statistical significance, the significance level is set at 5%, and ITT (intention-to-treat: intent-to-treat analysis) analysis and PP (per protocol) analysis are conducted for all data analyses. ITT analysis is applied in principle.

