#### Analysis of efficacy

2.10.4

For the primary (VAS) and secondary (SF-MPQ, WOMAC) outcomes, we will evaluate the difference of time and groups, and an interaction between the time and the groups using repeated-measure 2-factor analysis. If a significant interaction between the time and the groups was observed, we will use contrast analysis to compare individual differences between levels of the time and the groups.

For the other variables, we will evaluate the difference of the time using repeated-measure ANOVA test. When the variable measurement was implemented before and after treatment, we will calculate the change within the time, and evaluate the difference between the groups using Student *t* test as a parametric test, or Mann–Whitney test as a nonparametric test.

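### Feasibility and planning data are stated aims but have no defined outcome or analysis, while efficacy is tested at 5% in an unsized pilot with time-point contrasts that depend on a significant interaction

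*Protocol article*

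**What the plan says.** Section 2.1 of the protocol article gives three aims. The first is a comparison: "The aims of this pilot trial are to compare pain improvement between the TEA and the acupuncture groups with knee osteoarthritis". The other two are "to establish the feasibility of future TEA research, and to provide clinical evidence of the basic data before the large sample size study". The abstract and the Discussion repeat the feasibility purpose.

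Section 2.10.1 calls the trial a pilot and says that, "rather than following the separate sample counting criteria, 20 participants were selected (20% dropout rate considered) for the experimental and control groups".

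Section 2.5 names VAS as the primary outcome and SF-MPQ and WOMAC as secondary outcomes, each measured before treatment, at weeks 3 and 6, and four weeks after treatment ends. Section 2.10.2 adds: "For statistical significance, the significance level is set at 5" per cent. It also makes intention-to-treat the main analysis, with last observation carried forward (LOCF) for drop-outs.

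Section 2.10.4 states the efficacy analysis. "For the primary (VAS) and secondary (SF-MPQ, WOMAC) outcomes", it tests time, group and their interaction in a repeated-measures two-factor analysis. Contrasts between levels of time and group follow only when the interaction is significant.

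Other sections also bear on the point. Laboratory safety tests are in 2.6, adverse-reaction comparisons in 2.10.5 and descriptive baseline summaries in 2.10.3.1. Section 2.7 has the investigator record completion and the reasons for discontinuation.

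**The concern.** An aim in section 2.1 should have a counterpart among the outcomes and in the analysis. The pain comparison has one; feasibility does not. Recruitment, eligibility, attendance, retention and data completeness are not listed as outcomes or analysed, and no result is named that would favour, change or stop the larger trial.

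The planning aim is weakened in a second way. The next trial needs a VAS difference at a defined time, a standard deviation, and the uncertainty of both. Under section 2.10.4 the time-point contrasts appear only after a significant interaction, which a small unsized sample may well miss. The plan would then give no group difference at week 6. The change-score comparison in the second paragraph of 2.10.4 is written for variables other than VAS, SF-MPQ and WOMAC, so it does not fill the gap.

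Feasibility is a live question here. The arms differ in burden (6 weekly sessions against 12 twice-weekly sessions, section 2.4) and the trial is open-label (section 2.9), so attendance and drop-out may differ by arm.

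**Working it through.** **Aims against outcomes and analyses**

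- Compare pain: VAS, SF-MPQ and WOMAC in 2.5, tested in 2.10.4. Covered.
- Feasibility: nothing in 2.5 and nothing in 2.10. Completion is recorded under 2.7 but is not attached to an outcome, criterion or analysis.
- Basic data for the larger trial: clinical scores at four times are collected, but the time-point difference depends on the interaction test and the article plans no confidence interval.

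**The plan's own figure**

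The article gives no effect size, SD or power, so 20 per arm cannot be derived. The only check is drop-out: 20 × (1 − 0.20) = 16 completers per arm. The figure 16 is back-calculated, not stated.

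**Inputs**

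- n = 20 per arm (intention-to-treat with LOCF) or 16 per arm (completers).
- α = 5%, taken as two-sided because sidedness is not stated.
- Standardised differences d = 0.5 and 0.8, assumed.

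**Power of a simple two-group t test**

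Non-central t with 2n − 2 df and non-centrality d × √(n/2).

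| n per arm | d = 0.5 | d = 0.8 | d for 80% power |
|---|---|---|---|
| 20 | 34% | 69% | 0.91 |
| 16 | 28% | 59% | 1.02 |

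For 80% power at d = 0.5, about 64 per arm would be needed.

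**Precision of a group difference**

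Half-width in SD units = t(0.975; 2n − 2) × √(2/n).

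- n = 20: 2.024 × 0.316 = 0.64 SD.
- n = 16: 2.042 × 0.354 = 0.72 SD.

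If the VAS SD were 2 cm (an assumption), this is 1.28 to 1.44 cm. Over SDs of 1.5 to 2.5 cm it is 0.96 to 1.60 cm with 20 per arm and 1.08 to 1.81 cm with 16.

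**Precision of the SD**

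95% limits as multiples of the estimate: √(df/χ²(0.975)) to √(df/χ²(0.025)).

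- 38 df: 0.82 to 1.29. The next trial's n scales with SD², so it is known to a factor of 0.67 to 1.66.
- 30 df: 0.80 to 1.34, so a factor of 0.64 to 1.79.

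The 38-df figures count carried-forward values as if observed, so they are the optimistic end.

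**Precision of a feasibility rate**

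Retention of 32/40 = 80%, used as an illustration, has an exact 95% interval of 64% to 91%.

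**The case against.** The strongest defence is that the document is candid. It calls itself a pilot, says the sample was not calculated, and presents its results as input to a larger trial. Comparing pain is the first-listed aim, and a VAS primary outcome serves it. Progression thresholds, confidence intervals and exploratory labels are often left to a full protocol or analysis plan, neither of which is shown. The power figures describe a single-time-point t test, whereas the plan uses repeated measures.

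Much of this stands. Low power in a declared pilot is not itself an error. The main analysis has up to 20 per arm, so the 16-per-arm figures are the less favourable case. Repeated measures or baseline adjustment could raise power, by an amount that cannot be computed because the article gives no correlation. The exact thresholds may sit elsewhere.

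It does not remove the point. The article does state its aims, its outcome list and the condition on the contrasts, and these do not fit together.

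A reader might go further and infer that efficacy tests are the only planned output, that no feasibility data are collected, or that the trial cannot meet any of its aims. The documents do not support this: safety and descriptive analyses are planned, completion and discontinuation reasons are recorded, and the pain comparison is addressed, though weakly. Nor do they require feasibility to become the primary outcome, which would demote the first-listed aim.

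**Conclusion.** The point holds for the feasibility and planning aims only. As written, the trial has no defined feasibility result and may end without a planned group difference at any time point.

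On the assumed effect sizes and a two-sided t test, 80% power needs a difference of about 0.91 SD with 20 per arm, or 1.02 SD with 16 completers. No margin is set against the active comparator, so a non-significant result could not be read as similarity. The article does not claim that it would be.

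The same 40 participants can still give useful estimates: a difference to within about 0.64 to 0.72 SD, an SD to within about 0.80 to 1.34 times its estimate at worst, and a retention rate with an interval like the one shown. The sample can serve these aims if the plan asks for them. This should be changed, but it does not undermine the design.

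**What to change.** Keep VAS as the primary clinical outcome and make these changes:

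1. Add feasibility outcomes to section 2.5: recruitment rate, eligible out of screened, sessions attended out of 6 and out of 12, and retention and VAS completeness at the final follow-up. Report the attendance and retention measures by arm.
2. Set progression criteria for the larger trial before any data are seen.
3. In section 2.10.4, report the week-6 VAS difference and the pooled SD with 95% confidence intervals whatever the interaction test shows.
4. In section 2.10.2, label all p-values exploratory and state that no confirmatory efficacy conclusion and no equivalence conclusion will be drawn.

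No new visits or measurements are needed. The counts should come from the screening contacts in section 2.2, the visit records and the completion records in section 2.7. The cost is a more modest headline claim and a little extra analysis.

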### Study design

2.2

We will conduct a single-institution, randomized controlled pilot trial to compare the efficacy and safety of TEA with acupuncture on knee osteoarthritis.

A total of 40 participants diagnosed with knee osteoarthritis will be recruited from Daegu Oriental Hospital through advertisements. The recruitment period will run from the date of Institutional Review Board (IRB) approval to December 31, 2020. The investigator will have an interview with every potential participant by telephone and schedule screening visits. During the screening visits, every potential participant will be informed in details, ample opportunities to know about all foreseeable results will be given, and written consents will be obtained from the participants. A random assignment will be performed to divide the experimental group and the control group. The probability of being assigned to the 2 groups will be the same. The experimental group will receive TEA treatment on the knee region. The control group will receive commonly used acupoints for knee osteoarthritis treatment. The visit date will be recognized 3 days before and after the visit date and carry on for 10 weeks. A flowchart of the study is illustrated in Fig. 1, and the clinical trial schedule for treatment and outcome measurement is presented in Table 1.

**Figure 1 F1:**
[figure not shown]
Study flow chart.

**Table 1 T1:**
[figure not shown]
Schedule for the treatment and outcome measurements.

### Participants

2.3

#### Inclusion criteria

2.3.1

(1)50 years old and above(2)Morning stiffness to last less than 30 minutes(3)Applicable for VAS 4-7(4)Kellgren-Lawrence grade 2 to 3 on knee X-ray(5)Knee pain lasting more than 3 months(6)Consenting participants

#### Exclusion criteria

2.3.2

(1)Those who had surgery on the knee due to osteoarthritis or other injuries(2)Those who received intraarticular injection of phototherapy, steroids, or hyaluronic acid within the last 3 months(3)Those with serious psychiatric problems(4)Those in need of adrenocortical hormones or other nonsteroidal anti-inflammatory analgesic drug treatment due to other medical conditions(5)Those with skin allergies, skin ulcers, or skin infections(6)Insulin injecting diabetic patients(7)Those using anticoagulants(8)Those elevated liver function tests (ALT, AST), more than 3 times the normal value(9)Those with abnormal findings on renal function test(10)Those who are deemed inappropriate for the study by the person in charge

#### Randomization

2.3.3

Block randomization will be performed, the size of the block will be 4, then the experimental and control groups will be 2:2 for each block, the randomization codes will be assigned between the groups, and will be proceeded as a pilot study. Random numbers were generated by an independent statistician. Sealed opaque assignment envelopes were used for allocation concealment. Once the clinical trial starts, each participant, who meets the selection criteria, will be assigned to the experimental and control groups according the randomization code.

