### Blinding

2.9

This is an open-label study comparing TEA with acupuncture treatment. It was not possible to design a double-blind for both the practitioner and the participant in this study, without revealing either the TEA or the acupuncture treatment, because of the intervention characteristics and area of application of the thread embedding treatment. In addition, the 2 groups have different number of visits.

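### A fixed, published block size of 4 in a single-site open-label trial would let a recruiter who tracks assignments deduce about a third of the allocations

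*Protocol article*

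**What the plan says.** Section 2.3.3 (Randomization) sets one block size and the split within it: "Block randomization will be performed, the size of the block will be 4, then the experimental and control groups will be 2:2 for each block". It adds that an independent statistician produced the random numbers and that sealed opaque envelopes conceal the allocation.

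Section 2.2 (Study design) places the trial at one site: "We will conduct a single-institution, randomized controlled pilot trial". It also sets a 1:1 ratio: "The probability of being assigned to the 2 groups will be the same". No stratification factor is named anywhere. The investigator telephones every candidate and arranges the screening visits. Information and written consent come before random assignment in the order of the text.

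Section 2.9 (Blinding) reads "This is an open-label study comparing TEA with acupuncture treatment" and adds "In addition, the 2 groups have different number of visits". Section 2.4 gives the visit pattern as 6 sessions of TEA against 12 of acupuncture. The abstract gives 40 participants, 20 per arm.

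Section 2.3.2 (Exclusion criteria) is mostly objective, but item 10 leaves exclusion to the judgement of the person in charge.

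**The concern.** Allocation concealment has two parts: the next assignment must not be visible, and it must not be deducible. The envelopes and the independent statistician deal with the first. A known, constant block size weakens the second. Once either arm has used its two places in a block, the rest of that block is fixed. With one site, one implied sequence and open treatment, a member of staff can know all earlier assignments in order.

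If the person deciding whether and when to enrol someone can foresee the arm, patients with a better or worse outlook can drift towards one arm, deliberately or not. The primary outcome is a VAS marked by an unblinded participant (2.5.1.1), so blinded assessment offers no second safeguard. Comparing pain between the groups is a stated aim (2.1) and is tested (2.10.4), and the result is meant to inform a larger trial.

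**Working it through.** The plan states no predictability figure, so there is none to reproduce. As a consistency check, 40/4 = 10 complete blocks, each 2:2, gives 20 per arm, which agrees with the abstract.

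**Inputs.** Block size 4, split 2:2 (2.3.3); N = 40 (abstract, 2.2); one sequence (2.2, no strata named); past assignments visible (2.9). Write A for TEA and B for acupuncture.

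**Step 1: allocations known with certainty.** There are C(4,2) = 6 equally likely sequences. A position is certain when one arm has already used both its places. For the best guess, name the arm that lags, and count 1/2 when the arms are level.

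| Sequences | Number | Certain positions | Expected correct guesses |
|---|---|---|---|
| AABB, BBAA | 2 | 2 (3rd and 4th) | 0.5 + 0 + 1 + 1 = 2.5 |
| ABAB, ABBA, BAAB, BABA | 4 | 1 (4th) | 0.5 + 1 + 0.5 + 1 = 3.0 |

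- Mean certain per block: (2×2 + 4×1)/6 = 8/6 = 1.333, and 1.333/4 = 33.3%.
- Over 10 blocks: 13.3 of 40 expected. The minimum is 10 (25%) and the maximum 20 (50%). The probability of 11 to 16 is about 0.96.

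**Step 2: best-guess rate.** (2×2.5 + 4×3.0)/6 = 17/6 = 2.833 per block, and 2.833/4 = 70.8%, against 50%. This rule needs only a tally of the arms, not the block size, because every completed block is balanced.

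**Step 3: after varying the block size.** A simulation used 3,000 sequences of 40. It assumed that sizes 4, 6 and 8 are equally likely, and that the recruiter knows this set but not the order. It gave 2.2% certain and a best-guess rate of 67.6%. The lagging-arm rule gives nearly the same rate by enumeration: (2.833 + 4.100 + 5.329)/18 = 68.1%. For comparison, single known sizes of 6 and 8 leave 25% and 20% certain.

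**Step 4: what this could do to the estimate.** Suppose, as an assumption, that a recruiter shifts the expected VAS change of the next patient by +η or −η according to the guess, at every allocation where the arms are not level. Correct minus wrong guesses average 2.0 − 0.333 = 1.667 per block. With 2 patients per arm per block, the bias is 1.667/2 = 0.83η. In general it is 2(2H − 1)η for a hit rate H. With H = 0.681 it is 2 × 0.362 = about 0.72η.

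| Assumed η (cm) | Fixed 4 (cm) | Mixed 4/6/8 (cm) |
|---|---|---|
| 0.25 | 0.21 | 0.18 |
| 0.5 | 0.42 | 0.36 |
| 1.0 | 0.83 | 0.72 |

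These values apply only to steering on prognosis for change. A shift that is equal at all visits cancels in the time-by-group interaction of 2.10.4 and in change from baseline.

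**The case against.** The best case for the plan is this. The sequence comes from an independent statistician, the envelopes are opaque and sealed, and consent and eligibility already precede assignment in the text. Most criteria are objective: age, radiographic grade, liver tests, anticoagulants, insulin, earlier surgery. The article does not say that recruiting staff know the block size or follow the sequence, and a condensed article may leave the separation of roles to the full protocol. This is a 40-patient pilot without a formal sample size calculation (2.10.1), and small fixed blocks keep the arms balanced if recruitment stops early. Varying the block size also barely lowers the best-guess rate.

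Much of that stands, and it rules out several stronger readings:

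- A reader might infer that concealment has failed. The documents show only that deduction is possible.
- A reader might treat the VAS 4–7 window as investigator discretion. Section 2.5.1.1 has the participant mark the line and the investigator measure it, so this is a weak route. Exclusion 10 and the timing of screening visits are the main ones.
- A reader might take a figure in centimetres as the bias of the primary result. Any such figure rests on an assumed η, and the planned interaction test removes a shift common to all visits.
- A reader might think that mixed blocks cure the bias. They remove certainty and little else.

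What the objection does not remove is that the article itself fixes and publishes the block size. This is not a detail left to another document, and envelopes cannot hide what can be deduced. Pilot status limits the consequence, but the between-group pain comparison remains an aim.

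**Conclusion.** The concern holds as a conditional risk. For someone who knows the block size and has followed all earlier assignments in order, the stated scheme makes on average 33.3% of allocations certain (about 13 of 40, at least 10 in every realisation), and a tally guesses 70.8% correctly. Both figures are exact expectations under 10 complete 2:2 blocks in one sequence.

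Whether anyone would act on this, and by how much, cannot be read from the article. The modelled bias of 0.83η is therefore an illustration and should be quoted only as a range, together with its after-fix value of about 0.72η. This is an inexpensive design improvement worth making, not a demonstrated flaw in the trial's result.

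**What to change.** - Have the independent statistician generate the list with randomly varied block sizes, for example 4, 6 and 8. Section 2.3.3 uses the past tense for the list and the envelopes, so they may already exist. If enrolment has begun, replace only the remaining part, starting at the end of a completed block.
- Withhold the sizes from recruiting staff and from the protocol that they see. That text need say only that permuted blocks of varying size are used.
- State that each envelope is opened only after consent and eligibility have been recorded. The order is already implied in 2.2 and 2.3.3; the explicit recording step is what is new.

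**Gain.** Certain knowledge falls from 33.3% to about 2%. The best-guess rate falls only from 70.8% to about 68%, so the steps around envelope opening still matter.

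**Cost.** A new list and a new set of envelopes. The arms can differ at the end by up to half the largest block, which is 4 patients for a block of 8, against 2 for a block of 4. At 22/18 the relative efficiency is 4 × 22 × 18/40² = 1584/1600 = 0.99, a loss of about 1%.
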